### Randomization

Enrolled dyads will undergo 1:1 block randomization by each study clinic performed by the Anglia Ruskin Clinical Trials Unit (ARCTU) to assign them to the intervention group or the control group. Randomization will be undertaken using an internet-based randomization system setup by ARCTU on the TENALEA system provided by FormsVision BV. The system stores the predetermined sequence of randomization; this list is not available to the investigators.

### Intervention: the Support Monitoring and Reminder Technology for Mild Dementia Platform

Our intervention strategy, which aims to improve the QoL of PwMCI, is based on the use of a single or multiple function that the SMART4MD app enables. The rationale behind and description of the functionalities of the SMART4MD app are presented in detail in a separate document (Multimedia Appendix 1). Briefly, participants in the intervention group will be provided with a data-enabled computer tablet preinstalled with the SMART4MD app. The tablet will be configured in such a way that it is not possible for participants to download any other app or software onto the tablet.

SMART4MD is a general electronic health app that has been adapted specifically for MCI through a structured process involving the participation of PwMCI and their informal carers and health care professionals. Focus groups were conducted with PwMCI and their informal carers, and interviews were conducted with health care professionals. The app can run both on tablet and mobile phone devices adopting the Android operating system but is specifically optimized for tablet devices as opposed to smaller screen mobile phone devices.

The core functionalities of the app are based on reminders (medication, appointments with health care providers, and meeting up with family and friends), cognitive supporting activities (clock, calendar, brain games, and photos) and optional status and health information sharing with family and informal carers (including mood and specific health problems such as headaches).

The app allows the participant to share health information to other people of their choice (relatives or research team) by email. The participant can select what kind of information he/she can share and to whom he/she wants to send this information.

An important feature of SMART4MD is its personalization facility: main users (PwMCI and informal carers) will be able to switch on/off or change various features and information-sharing possibilities.

The app is intended to be used daily at home, mainly by the PwMCI themselves, with the help of their informal carers when needed.

### Training and Support for App Users

The SMART4MD user training across the trial sites will be delivered in the most uniform way possible, minimizing bias. Support during the trial regarding the use of the app will be provided, and each center will nominate 1 individual to lead the support for participants recruited and assigned to the intervention group, helping users in their own language. On the day of delivery of the tablet, a training session is held for both the subject and the caregiver, with explanations of how the tablet and the app works.

In addition, a paper-based manual is delivered on the introductory meeting as a complement to the verbal introduction. The manual has been developed with an emphasis on the parts of the tablet and app, where users in the feasibility study experienced difficulties.

Finally, throughout the clinical trial, participants have a contact person in each site with whom they can consult regarding their doubts and technical problems.

The hours and limits of responsibility of this support will be standardized across trial sites. The support will be delivered at clinical visits or via email or phone calls.

### Control Group

The control group will only receive their TAU. There are different conditions and diseases and the treatment can vary widely among the participants. In addition, there are different health care systems among study centers. In any case, the participants in the control group will receive the TAU that they would receive at their care center regardless of the study.

### Outcomes in Persons With Mild Cognitive Impairment

#### Primary Outcome

##### Health Related Quality of Life

Health related quality of life of PwMCI will be measured using the total score of the QoL-AD questionnaire [33,38,39]. This is a 13-item measure, which has been specifically designed to measure QoL in individuals with dementia from the perspective of both the PwMCI and the informal carer. It includes questions related to the interpersonal, environmental, functional, physical, and psychological status of the person with dementia, and thus, it is a global measure for QoL. QoL-AD will be assessed via an interview with PwMCI and via self-completion by informal carers.

#### Secondary Outcomes:

##### Adherence to Prescribed Medication: Doses and Pill Count

Adherence to prescribed medication will be assessed by comparing the PwMCI’s documented prescription for medications with the number of pills taken (or if medication is not in pill form, pill equivalents) in the 30 days before the assessment day.

This assessment will be undertaken by a Principal Investigator PI or delegate at the 6-, 12- and 18-month visits. PwMCI and informal carer dyads will be asked to bring any documentation related to their prescription history for all medications and all the remaining pills (or pill equivalents) and empty medication packaging they have from the previous 30 days so that the researcher can undertake the medication count.

The dose/pill count is the number of pills or doses taken divided by the number of pills or doses prescribed, multiplied by 100 (expressed as a percentage) [40,41]. According to Haynes et al recommendations, a good adherence is considered when the result of counting is between 80% (a 20% of doses/pills missed) and 110% (the patient takes 10% more doses/pills) of doses/pills prescribed. We will select a maximum of 2 drugs for each participant in the pill count.

##### Cognitive Function

It will be measured by the MMSE [42]. It is also used to estimate the severity and progression of cognitive impairment and to follow the course of cognitive changes in an individual over time. To be included in the trial, individuals must score between 20 and 28 points on the scale. The use of an MMSE cutoff value of 28 is not common and has some risks but has been used in other studies [43]. O’Bryant et al [44] showed that an MMSE cutoff score of 28 gave the best sensitivity and specificity for detecting mild dementia in a population with self-reported memory complaints.

##### Functional Decline

The EuroQol-5D (EQ-5D) is a self-completion questionnaire that consists of 5 questions plus a scale where the participant rates their health state on a scale of 0 to 100. EQ-5D has been shown to correlate well with QoL-AD, indicating that the 2 measures are compatible and can be used side by side [38].

##### Service Utilization

Attendance at health care appointments and admissions to health care institutions will be collected from health management systems in the participating regions.

#### Independent Variables-Covariables

##### Sociodemographic Data

Age, gender, education, whether participant lives alone, marital status, and relationship with the informal carer are the sociodemographic variables.

##### Medical History of Persons With Mild Cognitive Impairment

These include family antecedents such as Alzheimer disease, Parkinson disease, other dementing illness; Comorbidity International Classification of Diseases-10; Current Treatment according to The Anatomical Therapeutic Chemical Classification System Information about dementia: diagnosis of dementia, type of dementia, if they have undergone a magnetic resonance imaging scan, and if they are using any pharmacological treatment for their dementia.

##### Depression

The GDS-15 [37] will be used as an exclusion criterion, screening for depression. If participants score above 11, they will be excluded from the trial.

The GDS is commonly used as a routine part of a comprehensive geriatric assessment. The grid sets a range of 0 to 4 as “normal,” 5 to 8 as “mildly depressed,” 9 to 11 as “moderately depressed,” and 12 to 15 as “severely depressed.”

##### Familiarity With Comparable Technological Devices

This will be assessed via a questionnaire of 6 questions tailored to this study, covering both prior and current experience of using internet and mobile technology in general and, specifically, apps with particular relevance to SMART4MD functionality (Multimedia Appendix 2). It will also include an instrument to measure general attitudes and feelings toward technology [45].

##### User Behavior

In the intervention group, the following data will be collected from the platform: date and time of any interaction with the SMART4MD app, length of interaction, and the functions used during the interaction.

### Outcomes in Carers

#### Secondary Outcomes

##### Carer Burden

The Zarit Caregiver Burden Interview (ZBI-12) [46,47] will be used to evaluate informal carers’ burden. The ZBI-12 is a 12-item scale with each answer chosen from a 5-point Likert scale. It is a shortened version of the original scale that was developed specifically for informal carers of PwMCI and covers issues such as carer stress and the degree to which caring is affecting their health and social life. It will be administered via interview with the informal carer.

#### Independent Variables-Covariables

##### Sociodemographic Data

Age, gender, education, whether participant lives alone, marital status, and familiarity with comparable technological devices are the sociodemographic variables.

### Follow-Up Visits

There will be 3 follow-up visits at 6, 12, and 18 months after baseline interview. A summary of visits’ assessments is shown in Table 1. In addition, to measure medication adherence, there will be a preadherence phone call in each follow-up visit (30 days before the visit).

**Table 1 table1:** Schedule of events.

Events, assessments, and data collection	Screening	Baseline	Tablet delivery	Month 6 ±18 days	Month 12 ±18 days	Month 18 ±18 days
Informed consent (PwMCI^a^ and informal carer)	X^b^	—^c^	—	—	—	—
Review of inclusion and exclusion criteria (PwMCI)	X	—	—	—	—	—
Demography (PwMCI and informal carer) and medical history (PwMCI)	—	X	—	—	—	—
Introduction and training for Support Monitoring and Reminder for Mild Dementia (intervention group only, PwMCI and informal carer)	—	—	X	—	—	—
Geriatric Depression Scale (PwMCI)	X	—	—	X	X	X
Mini-Mental State Examination (PwMCI)	X	—	—	X	X	X
Quality of Life in Alzheimer's Disease scale (PwMCI)	—	X	—	X	X	X
Instrumental Activities of Daily Living (PwMCI)	—	X	—	X	X	X
Adherence to prescribed medication (PwMCI)	—	X	—	X	X	X
EuroQol-5D (PwMCI and informal carer)	—	X	—	X	X	X
Attendance at appointments and admissions (PwMCI)	—	X	—	X	X	X
Familiarity with tech survey (PwMCI and informal carer)	—	—	X	—	—	—
QoL-AD on behalf of PwMCI (informal carer)	—	X	—	X	X	X
Zarit Caregiver Burden Interview (informal carer)	—	X	—	X	X	X
User satisfaction survey (intervention group only, PwMCI, and informal carer)	—	—	—	X	X	X
User behavior (intervention group only, informal carer, and PwMCI)	—	—	—	X	X	X

^a^PwMCI: persons with mild cognitive impairment.

^b^The instrument is used at this time point.

^c^The instrument is not used at this time point.

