**Methods:**

A pragmatic, multicenter RCT is being conducted in Spain, Sweden, and Belgium. The targets for recruitment are 1200 dyads—split into an intervention group and a control group that are in usual care. Intervention group participants will be provided with a data-enabled computer tablet with the SMART4MD app. Its core functionalities, intended to be used daily at home, are based on reminders, cognitive supporting activities, and sharing health information.

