#### Secondary Outcome Analyses

The comparison between intervention group and control group for continuous variables will be analyzed with the same method described above, and categorical variables will be analyzed using Fisher exact test.

Regression analysis will be used to assess the relationship between the primary and secondary outcome measures and the Technology Familiarity Score to analyze whether prior experience of technology has an effect on the outcomes. Furthermore, a regression analysis will be used to assess the relationship between the primary and secondary outcome variables and the usage variables to indicate which aspects of the computer tablet use most affected the outcomes.

A user-behavior analysis will be performed to assess how users interact with the platform and how their behavior affects its efficacy. Specifically, we will assess and analyze the frequency of access to the SMART4MD app, the length of this interaction, and the quality of the inputs provided. These data will be correlated with users’ reminder schedules to explore differences between proactive and reactive use of the platform and will be followed over time to understand how increasing familiarity with the platform affects user behavior. In addition, the data will be used to improve the SMART4MD app, if necessary, to optimize user interaction. The results of the usability tests will be analyzed using statistical methods to quantify the error rate, effectiveness, and learning curve of the SMART4MD app and functions. For this, the intervention group will be asked to perform specific tasks with the app, and different interaction parameters will be measured such as number of taps, reaction time, time to target, time to accomplish, etc.

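### The schedule gives control dyads no time point for the technology-familiarity survey, although familiarity is a covariable without arm restriction and its planned regression is not limited to one arm

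*Protocol article*

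**What the plan says.** The schedule of events (Table 1, under Follow-Up Visits) has a row "Familiarity with tech survey (PwMCI and informal carer"). Its single mark is under Tablet delivery. Screening, Baseline and Months 6, 12 and 18 carry dashes, and the table note defines a dash as "The instrument is not used at this time point".

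The only other mark in that column belongs to "Introduction and training for Support Monitoring and Reminder for Mild Dementia (intervention group only, PwMCI and informal carer").

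The intervention section says that "participants in the intervention group will be provided with a data-enabled computer tablet preinstalled with the SMART4MD app". The training section adds: "On the day of delivery of the tablet, a training session is held for both the subject and the caregiver". Of the comparator, the Control Group section says: "The control group will only receive their TAU". The Recruitment section places randomization directly after signed consent.

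Familiarity is listed under the independent variables and covariables for the person with mild cognitive impairment, and again among the carer's sociodemographic variables. Neither listing names an arm. The questionnaire covers past and present use of technology and includes an instrument on attitudes and feelings toward it. Secondary Outcome Analyses then plans a regression relating the primary and secondary outcomes to the Technology Familiarity Score, "to analyze whether prior experience of technology has an effect on the outcomes", again without naming an arm.

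**The concern.** The schedule and the analysis text do not fit together. A covariable listed without arm restriction, and a regression that is not confined to one arm, need a score from both groups. The only scheduled collection point is one that control dyads appear not to have.

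Two things are at stake. The first is interpretation. With scores from the intervention arm alone, an association between familiarity and quality of life could mean that people used to technology fare better with or without the app, or that they gain more from it. The second is timing. A covariate is best measured before allocation. Here the current-use and attitude items would be answered by people who know that they are receiving a tablet, on the day they are trained to use it.

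The question bears on the trial's own rationale. The Discussion names this age group's unfamiliarity with digital devices as the challenge to adoption.

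**Working it through.** The protocol gives no figure for this point to reproduce. The check is a side-by-side reading, one count and one line of algebra.

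**Step 1. Who has a time point?**

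| Table 1 column | Survey marked? | Contact for controls? |
|---|---|---|
| Screening | no | yes |
| Baseline | no | yes |
| Tablet delivery | yes | none described |
| Months 6, 12, 18 | no | yes |

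The survey is marked in 1 of 6 columns. Of the columns that clearly apply to controls, 0 are marked. A dash is defined as non-use, so the absence at Baseline is a positive statement and not a detail left out of a condensed article.

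**Step 2. Is the contact after randomization?** Randomization follows consent (Recruitment). Tablets go to the intervention group (intervention section), so delivery depends on allocation and must come after it. Marks before randomization that can be identified as such: 0.

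**Step 3. How many dyads have a score?** Inputs: 1200 dyads (Sample Size) and 1:1 allocation (Randomization).

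- Per arm: 1200 / 2 = 600.
- Scores as scheduled: at most about 600 in the intervention arm and 0 of about 600 in the control arm, so at most 600 / 1200 = 50% of dyads.
- With the 20% dropout used in the sample-size section: 600 × 0.8 = 480 intervention dyads with both a score and an 18-month outcome.

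**Step 4. What can a one-arm regression estimate?** Let A be arm (1 = intervention), F the familiarity score and Y the outcome:

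E(Y) = b0 + b1·A + b2·F + b3·A·F

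Here b2 is the general association of familiarity with outcome, and b3 is the change in the intervention effect per unit of familiarity. In the intervention arm A = 1, so

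E(Y | A = 1) = (b0 + b1) + (b2 + b3)·F

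Only the sum b2 + b3 can be estimated. If F is never observed when A = 0, no sample size separates the two.

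**Step 5. What do the labels suggest was intended?** Three rows of Table 1 are restricted to the intervention group: training, user satisfaction and user behavior. The survey row is not. The User Behavior section limits its data to the intervention group, while the familiarity section has no such limit. Carer familiarity is listed with the sociodemographic variables, and Table 1 collects demography at Baseline, yet the survey row shows a dash there. The labels point to both arms; the column points to one.

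**The case against.** The strongest reply is that nothing in the protocol states that Tablet delivery is an intervention-only contact. Table 1 shows arm restriction by row. If the column alone implied one arm, the restriction on the training row in that same column would be redundant. One could read the column as a contact at which both arms are surveyed and one is trained. The full protocol, which is not shown, might also say when controls answer. This stands as a limit on wording. A reader might infer that no control data will exist, but the documents support only that the schedule provides no control time point. They do not remove the conflict, because no section describes a delivery-time contact for a group that receives only usual care.

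Second, a reader might infer that the plan set out to test effect modification and cannot. The text does not support that. It asks whether prior experience affects outcomes and names no interaction. The regression planned next uses usage variables, which exist only in the intervention arm, so a within-arm association is a coherent if limited aim. What remains is that such an association cannot carry a broader reading.

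Third, a reader might infer that the whole score is distorted by allocation. Prior-experience items concern history, which allocation cannot change, although recall comes later. Only current-use and attitude items are exposed. The protocol does not say whether the survey precedes training that day, and no size of bias can be derived.

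Fourth, the score enters neither the primary comparison, nor the covariance analysis, nor the subgroup analyses, nor the sample size. This stands in full and limits the severity.

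**Conclusion.** The point holds as an internal inconsistency of moderate severity. Table 1 gives control dyads no time point for a survey that other sections treat as a covariable without arm restriction and enter in a regression without arm restriction. Followed literally, the schedule yields scores for at most about 600 of 1200 dyads, collects the current-use and attitude items after allocation is known, and leaves general prognosis and a different benefit from the app inseparable.

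This rests on two assumptions: that Tablet delivery is an intervention-arm contact, inferred from the intervention, training and control sections; and that allocation is equal and recruitment reaches its target. If controls are in fact surveyed at that contact, the missing-data and separability problems disappear. The timing after randomization would remain. The documents do not support any stronger claim that the primary result is at risk.

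**What to change.** - Schedule the survey for both arms before randomization: at Screening, or at Baseline if that visit precedes randomization. The article does not say whether it does, so the text should fix the order rather than only move the mark.
- Fit the familiarity regression in both arms, with arm, familiarity and their interaction. This lets the general association and any difference in the app's effect be reported separately.
- For dyads already randomized, a pre-randomization value cannot be recovered. Inclusion began in December 2017, recruitment was expected to end in February 2019, and the article is dated June 2019, so this may be most or all of them. Either collect the prior-experience items retrospectively in both arms, or limit the stated conclusion to an association within the intervention arm.
- If controls are already surveyed, say when in Table 1.

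The cost is one short questionnaire for control dyads (six questions plus the attitude instrument; the prior-experience items only if collected retrospectively), which can be given at a visit they already attend. The sample size and the primary analysis do not change.

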### Statistical Analysis

All analyses will be performed with the SPSS 25+ program (IBM Corp) [48].

#### Summary of Baseline Data and Persons With Mild Cognitive Impairment Progress Through the Trial

For continuous variables we will collect the mean, median, minima and maxima, lower and upper quartiles, and SD. Categorical variables will be summarized using counts and percentages. The progress of the PwMCI will be shown schematically with counts and percentages in a CONSORT diagram. The analysis will adopt the intention-to-treat principle.

#### Primary Outcome Analysis

The primary analysis will be the comparison of total QoL-AD score mean changes (at 18 months) between intervention group and control group using a 2-sample, 2-sided Monte Carlo permutation *t* test. The use of a permutation test will avoid the need for strong assumptions about the distribution of the data. Similarly, a bootstrap approach will be used to obtain the 95% confidence limits for the difference between the group means.

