### Sample Size

A total of 1200 dyads (PwMCI+carers) is the target for recruitment, divided over 2 groups: an intervention group, using the SMART4MD app, and a control group, not using the SMART4MD app. In this clinical trial, QoL is the primary outcome measure, measured by the QoL-AD total score [33]. This score is based on 13 four-point (1 to 4) items on a discrete visual analog scale. Recent papers [34] show the standard deviation (SD) of the total QoL-AD score approaches 7.

To detect a small effect size of 0.2 comparing 2 groups (intervention and control), using a 2-sided *t* test with a 5% statistical significance level, with a power of 80%, the minimum number of PwMCI required in each group is 394 (788 overall). If there would be a dropout rate of 20%, the number of PwMCI registered on the study would need to be 493 in each group (thus 986 overall).

On the other hand, one of our secondary objectives is to increase adherence to prescribed medication by 10% in the intervention group. If we consider that in people with dementia, the treatment adherence is between 44% and 99% [35,36], and assuming the less prevalence (44%), which we want to increase by 10%, with a power of 0.8 and a significance level of .05, we need 1174 subjects (20% dropouts included). Therefore, the sample size of this study is adequate to detect statistical and clinical differences between groups for the QoL-AD (primary outcome) and treatment adherence (a secondary outcome).

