#### Adjusted Analyses

A secondary analysis will be an analysis of covariance to compare the 18-month total QoL-AD score means, where the response variable will be the 18-month total QoL-AD score and the covariate will be the baseline total QoL-AD score. This analysis will provide a comparison of the 18-month total QoL-AD score means adjusted for the baseline total QoL-AD score. Again, the *P* value will be obtained using a Monte Carlo permutation method, and the 95% confidence limits for the adjusted difference between the means will be obtained using a bootstrap approach.

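### The primary QoL-AD analysis compares unadjusted change scores, although the more precise baseline-adjusted ANCOVA is already in the plan as a secondary analysis

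*Protocol article*

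**What the plan says.** Under Primary Outcome Analysis: "The primary analysis will be the comparison of total QoL-AD score mean changes (at 18 months) between intervention group and control group". The test is a two-sample, two-sided Monte Carlo permutation t test, with bootstrap 95% limits for the difference in means. Secondary Outcome Analyses carries the same method over to the continuous secondary outcomes.

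Under Adjusted Analyses: "A secondary analysis will be an analysis of covariance to compare the 18-month total QoL-AD score means". Baseline total QoL-AD is the covariate, and the permutation P value and bootstrap limits are kept.

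Sample Size cites earlier work for the only SD given: "the standard deviation (SD) of the total QoL-AD score approaches 7". The calculation itself is stated on a standardized scale: "To detect a small effect size of 0.2 comparing 2 groups (intervention and control"), at two-sided 5% and 80% power, from which "the minimum number of PwMCI required in each group is 394 (788 overall"). Allowing for 20% dropout this becomes 493 per group, 986 overall. The recruitment target is 1200 dyads, and the Randomization section gives 1:1 allocation. The article states neither an SD of the change nor a correlation between baseline and 18 months.

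**The concern.** Two things do not fit together well.

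First, the less precise of two fully specified analyses of the same data decides the trial. A change score subtracts the whole baseline value, whereas ANCOVA subtracts only the part that predicts the 18-month value. Unless r is 1, the change score carries avoidable noise. It also responds more to a chance baseline difference between the groups.

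Second, the only SD quoted belongs to the total score, while the primary statistic is a change. The SD of a change depends on r and equals the raw SD only at r = 0.5. If the standardized 0.2 was meant against the SD of 7, the stated power rests on an r that the article never gives.

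At stake are the width of the confidence interval for the main result and, for a small effect, the chance of detecting it.

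**Working it through.** **Inputs from the article.** SD of the total score about 7; standardized effect 0.2; two-sided alpha 0.05; power 80%; 394 evaluable per group; dropout 20%; target 1200 at 1:1 (Sample Size, Randomization).

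**Assumptions.** SD 7 at both visits; true difference 0.2 × 7 = 1.4 points; r varied from 0 to 0.7. The 1.4 points and r are not in the article.

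**Step 1: reproduce the plan.** A two-sample t test at d = 0.2 needs 393.4, hence 394 per group (power 80.1%). With dropout, 394 / 0.8 = 492.5, hence 493 per group and 986 overall. Both figures agree with the article.

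**Step 2: group size at the recruitment target.** 1200 / 2 × 0.8 = 480 evaluable per group.

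**Step 3: SD of each analysis.**
- Change score: 7 × √(2(1 − r))
- ANCOVA residual: 7 × √(1 − r²)
- Ratio of variances, ANCOVA to change: (1 − r²) / (2(1 − r)) = (1 + r)/2. This is 0.65 at r = 0.3, 0.75 at r = 0.5 and 0.85 at r = 0.7, so the variance is 35%, 25% and 15% lower.

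**Step 4: power for 1.4 points (two-sample t test with the SDs of Step 3).**

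| r | SD change | SD ANCOVA | Change, 394 | ANCOVA, 394 | Change, 480 | ANCOVA, 480 |
|---|---|---|---|---|---|---|
| 0 | 9.90 | 7.00 | 51% | 80% | 59% | 87% |
| 0.3 | 8.28 | 6.68 | 66% | 84% | 74% | 90% |
| 0.4 | 7.67 | 6.42 | 73% | 86% | 81% | 92% |
| 0.5 | 7.00 | 6.06 | 80% | 90% | 87% | 95% |
| 0.6 | 6.26 | 5.60 | 88% | 94% | 93% | 97% |
| 0.7 | 5.42 | 5.00 | 95% | 98% | 98% | 99% |

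A simulation of the change-score test gave 73% and 80% at 394 per group (r = 0.4 and 0.5), and 80% and 87% at 480.

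**Step 5: r at which the change score reaches 80%.** At 394 per group the largest SD that still gives 80% is 7.005, so r = 1 − 7.005² / 98 = 0.50. At 480 it is 7.734, so r = 1 − 7.734² / 98 = 0.39.

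**Step 6: chance baseline imbalance.** At 394 per group the standard error of the baseline difference is 7 × √(2/394) = 0.50 points. For a given imbalance, the change-score estimate moves by (1 − r) times that imbalance relative to ANCOVA. At r = 0.5 and an imbalance of one standard error this is 0.25 points, or 0.25 / 1.4 = 18% of the assumed effect.

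**The case against.** A reader might infer that the trial is underpowered, or that its 80% power holds only if r is at least 0.5. The article does not support either reading, for three reasons.

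- The 0.5 threshold belongs to the article's own calculation of 394 per group. At the 1200 target less 20% dropout the threshold is about 0.39, and r = 0.5 gives 87%.
- The effect is stated only as a standardized 0.2. Reading it against the SD of 7 is natural, because the two stand next to each other, but it is an inference. If 0.2 means SDs of the change, 394 per group gives 80% power at any r. The detectable difference in points is then undefined: with SD 7 it would be 1.7, 1.4 or 1.1 points at r = 0.3, 0.5 or 0.7.
- No r is given. Above 0.5 the change-score test exceeds 80% even at 394 per group.

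A reader might also infer bias, or two rival primary answers. Neither follows. A permutation test of change is valid under randomization, and the estimate is unbiased over repeated randomizations; sensitivity to baseline imbalance is a matter of precision given the imbalance that occurs. The article labels one analysis primary and the other secondary. The primary test also matches the stated hypothesis about change over 18 months, and the ANCOVA result would be reported in any case.

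All of this stands and limits the severity. It does not touch the efficiency argument: the ratio (1 + r)/2 is below 1 for every r below 1, whichever SD the 0.2 refers to.

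**Conclusion.** The point holds as one of efficiency, together with an effect size whose scale is not defined. With equal SDs at the two visits, ANCOVA lowers the variance of the primary comparison by 15% to 35% for r from 0.7 to 0.3, using data that the trial already collects. For a true difference of 1.4 points, ANCOVA has at least 80% power at 394 per group for every r of 0 or more. The change score needs r of at least 0.50 there, or about 0.39 at 480 per group, where r = 0.3 would give 74%. These power figures rest on the raw-SD reading of 0.2, on SD 7 at both visits and on an assumed r. A shortfall is therefore possible but not shown. Severity: moderate.

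**What to change.** By documented amendment, before any between-group analysis:

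1. Make the ANCOVA under Adjusted Analyses primary: 18-month total QoL-AD on group and baseline total QoL-AD, with the permutation P value and bootstrap 95% limits already planned there.
2. Keep the change-score permutation test as a sensitivity analysis.
3. Use the same baseline-adjusted form for continuous secondary outcomes that have a baseline value.
4. State under Sample Size that 0.2 refers to the raw-score SD of 7 (1.4 points), and that this SD is conservative for ANCOVA because its residual SD, 7 × √(1 − r²), never exceeds 7.

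The cost is small: the two analyses change rank and one sentence is added. Table 1 already schedules QoL-AD at baseline, so no further data or participants are needed, and the distribution-free inference is kept. Recruitment was expected to end in February 2019 and the article appeared in June 2019, so the change falls during follow-up; it should be dated and its reason recorded.
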